### Participants and setting

The study will be based in 100 general practices within the UK's MRC general practice research framework (GPRF). There are two major reasons why the use of such a network of practices is necessary. First, in this study it is important to have high-quality data on clinical behaviours. In our previous work, we have used routinely available (prescribing) data as our measure of performance, and we have experienced problems with the specificity of such measures [34]. Second, it is of fundamental importance to this study that we obtain as near as possible complete 'sets' of questionnaires from all relevant members of the primary care team in order to allow the production of robust collective team level values. Although in previous studies we have been successful in obtaining sufficient responses, these have usually been across a large number of practices with only one or two responses per practice. Practices will be recruited by postal invitation with telephone follow-up via the GPRF.

Participants will be all clinical and non-clinical members of the primary care team within each practice. We will collect information about the organisation and team functioning of the primary care team from both clinical and non-clinical team members and information relating to clinical behaviours from clinical team members. Six different aspects of care delivery for patients with diabetes will be examined: glycaemic control, BP control, foot examination, weight management, patient education, and self monitoring. Anonymous clinical records of patients in the study practices will provide the data on clinical variables. A random sample of 100 patients per practice will provide data on clinician behaviours.

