#### Clinician self-reported behaviour

Two measures of clinicians' self-reported behaviour that can be regarded as proxies for actual behaviour will be included in the initial theory-based questionnaire – behavioural simulation and behavioural intention. Behavioural simulation will be measured using the method we have used previously [27]. From literature and expert consensus we will identify elements reported to influence management of the clinical conditions. From this, clinical scenarios will be constructed describing patients presenting in primary care. Respondents will be asked to make decisions on the management of the patients described. Behavioural intention will be measured by three items worded in a standard manner (*e.g*., I intend to control the BP of my patients with diabetes rated on a seven-point scale from 'strongly disagree' to 'strongly agree'). Responses to the three items will be summed [55]. A third measure of self-reported behaviour will be used. After a period of 12 months a questionnaire will be sent to clinical staff asking them about their behaviour in relation to the same six aspects of care over the preceding twelve months.

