### Sample size

For the practice-held, QOF, and clinician self-reported data, the analysis program 'G Power' [56] (using the method described by Cohen [57]) has been used to investigate the sample size required for testing alternative regression models. In this approach, the effect size is defined as the proportion of variance accounted for by a set of predictor variables (anticipated to be 14) relative to the residual variance proportion. In this context, effect sizes of 0.02, 0.15 and 0.35 are considered to be 'small', 'medium' and 'large', respectively. For the analysis of practice level variables (practice behaviour and the aggregated intention and behavioural simulation variables) with 100 practices we will have 80% power to detect an effect size of 0.21 assuming a type one error rate of 5% and 14 predictor variables. Assuming a (worst case) response rate of 75%, we will have data from all relevant staff (100 practices, four GPs, three practice nurses, one practice manager, two receptionists) the estimated sample size will be around 750 which, assuming a type one error rate of 5% and 14 predictor variables will give us 80% power to detect an effect size of 0.03. Thus, in the analyses of individual level data we will have 80% power to detect effect sizes in the small to medium range, and at the practice level we will have 80% power to detect effect sizes in the medium to large range.

For the patient-reported data, making the conservative assumption that the estimated proportion is around 50% if we sample 25 patients per practice, the standard error associated with our estimate for each practice is 10%. We will approach 100 randomly selected patients per practice (10,000 patients in total), allowing for a 25% response rate to achieve a final sample size of 25 per practice.

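### The individual-level sample of about 750 counts managers and receptionists, who supply no clinician self-reported outcome; about 525 are analysable, giving about 71% power at f² = 0.03 rather than the stated 80%

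*Protocol article*

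**What the plan says.** The Sample size section covers three kinds of data: practice-held, QOF and clinician self-reported. Power is for a multiple regression with a "set of predictor variables (anticipated to be 14") and a type I error of 5%. Effect size is Cohen's f², explained over residual variance, with 0.02, 0.15 and 0.35 taken as small, medium and large.

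For practice-level outcomes, 100 practices are said to give 80% power at f² = 0.21. For individual-level data the section begins "Assuming a (worst case) response rate of 75%, we will have data from all relevant staff", lists "100 practices, four GPs, three practice nurses, one practice manager, two receptionists) the estimated sample size will be around 750", and says that this, "assuming a type one error rate of 5% and 14 predictor variables will give us 80% power to detect an effect size of 0.03". It concludes that individual-level analyses can detect effects between small and medium.

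Other sections say who provides what:

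- **Participants and setting:** organisation and team-functioning information comes from all staff, but "information relating to clinical behaviours from clinical team members".
- **Clinician self-reported behaviour:** intention and behavioural simulation are presented as measures of clinicians' own behaviour. For the third measure, "After a period of 12 months a questionnaire will be sent to clinical staff". Administration of data collection repeats that clinical staff receive this second questionnaire.
- **Statistical analysis:** the dependent variables from the survey instruments are intention and behavioural simulation.

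**The concern.** Practice-held and QOF data are at practice level, so the individual-level calculation can only serve the clinician self-reported data. A regression uses only respondents who have the outcome. Managers and receptionists give ratings of work, team and organisation, which are predictors in this design. They are not described as giving intention, simulation or 12-month behaviour data. Counting them makes the sample for those models too large.

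What is at stake is how individual-level results are read. Someone who takes the stated figure at face value would treat a null result as good evidence against an effect of f² = 0.03, when the clinician sample has less power at that value than stated.

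**Working it through.** **Inputs, all from the Sample size section unless noted.** 100 practices; 4 GPs, 3 nurses, 1 manager and 2 receptionists per practice; 75% response; 14 predictors; α = 0.05. The restriction of the outcomes to clinical staff comes from Participants and setting, Clinician self-reported behaviour, and Administration of data collection.

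**Formula.** Overall F test in multiple regression: u = 14, v = N − 15, noncentrality λ = f² × N. Power = P(F′(u, v, λ) > F₀.₉₅(u, v)).

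**Step 1: reproduce the practice-level figure.** N = 100, f² = 0.21: v = 85, λ = 21.0, power 80.2%. This matches the stated 80%. The alternative λ = f² × v gives 71.5% and does not match, so λ = f² × N is used below.

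**Step 2: reproduce the 750.** (4 + 3 + 1 + 2) × 100 × 0.75 = 750. The count matches exactly and includes (1 + 2) × 100 × 0.75 = 225 managers and receptionists.

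**Step 3: check the stated power at 750.** f² = 0.03: v = 735, λ = 22.5, power 88.5%, not 80%. With 750 respondents, 80% power is reached at f² = 0.0248, so 0.03 looks like that value rounded up. About 624 respondents would be enough for 80% power at exactly 0.03.

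**Step 4: clinicians only.** (4 + 3) × 100 × 0.75 = 525. f² = 0.03: v = 510, λ = 15.75, power 70.6%. The detectable f² at 80% power is 0.0357. The sample is 624 − 525 = 99 short of what 0.03 needs. Meeting that need from 700 clinicians would take a response of 624/700 = 89%.

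**Step 5: 12-month self-report linked to baseline predictors.** This needs a response at both waves. The article gives no second-wave rate, so 75% at each wave is an assumption. The overlap of two groups of 525 among 700 clinicians then lies between 525 + 525 − 700 = 350 and 525. If responses at the two waves are independent it is 700 × 0.75 × 0.75 = 393.75, about 394.

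| Sample | N | Power at f² = 0.03 | f² at 80% power |
|---|---|---|---|
| All staff, as counted | 750 | 88.5% | 0.025 |
| Clinicians, initial questionnaire | 525 | 70.6% | 0.036 |
| Linked, full overlap (assumed) | 525 | 70.6% | 0.036 |
| Linked, independent (assumed) | 394 | 54.3% | 0.048 |
| Linked, least overlap (assumed) | 350 | 48.0% | 0.054 |

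As R² = f²/(1 + f²), the detectable explained variance moves from 0.0248/1.0248 = 2.4% at 750 to 0.0357/1.0357 = 3.4% at 525.

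Every figure treats staff as independent. Clustering within practices would lower power further. The article gives no intraclass correlation, so no design effect is applied.

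**The case against.** The strongest reply is that little depends on this figure. The section's closing statement is that individual-level effects between small and medium are detectable, which on its own scale means 0.02 to 0.15. Every detectable value above, up to 0.054, lies inside that band. The Statistical analysis section also says that most dependent variables are at practice level, with individual predictors reduced to practice means. Intention and simulation are analysed in aggregated form there too, at N = 100, and that calculation reproduces. All of this stands, and it limits the point to one misstated figure. A reader might infer that the study as a whole is underpowered or that its qualitative conclusion fails; the document does not support either.

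A second reply is that 750 is a correct count of expected questionnaire respondents, and that all of them complete the work, team-climate and organisational-justice measures. This is also true, and 750 suits reliability and validity work on those measures. It does not rescue the power claim, because no individual-level regression outcome supplied by all staff is named.

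Third, 75% is called a worst case, so 525 is a floor. The stated power is nevertheless tied to that rate, and clinicians would have to respond at about 89% to reach 80% power at 0.03. Attached clinicians such as district nurses are also to receive questionnaires, but the sample-size count leaves them out and the protocol itself doubts that usable data can be had from them.

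Two further inferences should be resisted. The 54% for the 12-month outcome is not a figure the plan implies: it needs an independent second response of 75%, and with full overlap there is no further loss. Nor is the absence of a second-wave allowance an error in itself, since a condensed article may leave that to the full protocol. Finally, one might say that power falls from 80% to 71%. On the plan's own method the fall is from 88.5% to 70.6%, because 750 gives more than 80% at 0.03.

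**Conclusion.** The stated individual-level power is wrong on the protocol's own inputs. The outcomes concerned come from clinical staff only, so the expected sample is 525 rather than 750, power at f² = 0.03 is about 71% rather than 80%, and the detectable effect at 80% power is about 0.036. This rests on the protocol's staffing numbers, its 75% response, 14 predictors, a 5% type I error and independent observations.

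For the 12-month self-report linked to baseline, only a range can be given, and it depends on an assumed 75% response at each wave: 350 to 525 clinicians, power at 0.03 of 48% to 71%, detectable f² of 0.054 to 0.036.

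This is a minor correction of a stated figure. The choice of 100 practices, the practice-level power and the small-to-medium conclusion do not change.

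**What to change.** In the Sample size section:

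1. For individual-level models of intention and behavioural simulation, state about 525 clinicians (7 × 100 × 0.75) with 80% power at f² of about 0.036.
2. For the 12-month self-report linked to baseline, state the assumed second-wave response. With 75% at each wave, give 350 to 525 clinicians and a detectable f² of 0.054 to 0.036; if independence is assumed, about 394 and 0.048.
3. Say that these figures are before any design effect for clustering of staff within practices.
4. Keep 750 only for analyses of measures that all staff complete. If a power figure is quoted for that number, pair it correctly: 80% at f² of about 0.025, or about 88.5% at 0.03.

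The cost is a few restated figures. Recruitment, data collection and the practice-level analysis need no change.

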We will examine mediating and moderating effects of the predictor variables on the dependent variables. In principle, we will be dealing mainly with dependent variables measured at the level of the practice and predictor variables measured at either the level of the practice or the level of the individual. The theoretical models will be tested using standard multiple regression analysis and structural equation modelling. For predictor variables that are measured at the level of the individual, we will produce a summary statistic for the practice. We will use the practice mean and, in the multiple regression analysis, will weight by practice size. We will explore other summary statistics with weightings reflecting the relevant roles and responsibilities of the respondents.

In addition to the main study analysis, the patient survey will be reported in its own right, including a comparison with the healthcare commission data (available from their website), a comparison of the level of agreement between patients' and health professionals' perceptions and a comparison of patient perceptions and physiological measures of diabetes control.

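### The individual-level power figure, and the analysis named with it, make no allowance for staff being clustered in 100 practices; the practice-level main analyses are not affected

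*Protocol article*

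**What the plan says.** The Sample size section of the protocol article makes two separate power statements, both with 14 predictors and a 5% type I error rate.

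- **Practice level.** For practice behaviour, and for intention and simulation aggregated to the practice, "with 100 practices we will have 80% power to detect an effect size of 0.21".
- **Individual level.** At 75% response the staff count is built up as "100 practices, four GPs, three practice nurses, one practice manager, two receptionists) the estimated sample size will be around 750", and for this number "assuming a type one error rate of 5% and 14 predictor variables will give us 80% power to detect an effect size of 0.03". The section then concludes: "Thus, in the analyses of individual level data we will have 80% power to detect effect sizes in the small to medium range".

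Neither statement mentions an ICC or a design effect.

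The Statistical analysis section lists respondents' intentions and simulated behaviour among the dependent variables, and organisational structure among the predictors. Its statement of method is: "The theoretical models will be tested using standard multiple regression analysis and structural equation modelling". Around that sentence it says that the outcomes are mainly at practice level. It adds that predictors measured on individuals are reduced to a practice mean, with the regression weighted by practice size.

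**The concern.** The study is built on the idea that people in one practice share a team and an organisation. It measures team climate and organisational justice, and it seeks near-complete sets of questionnaires so that team-level values can be formed. A power figure that counts 750 colleagues as 750 independent observations does not fit that premise.

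The problem is greatest when a predictor takes one value for the whole practice (list size, booking interval, skill mix, a practice mean of team climate) and the outcome is each respondent's own intention, simulated behaviour or self-reported behaviour. The information about such a predictor then comes largely from the number of practices. Ordinary regression would give it too small a standard error. At stake are an optimistic detectable effect for the individual-level analyses, and organisational factors being called predictive of individual outcomes more often than the stated 5%.

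**Working it through.** **Inputs from the Sample size section.** 100 practices; 4 + 3 + 1 + 2 = 10 staff each; 75% response; 14 predictors; alpha 0.05; f² = 0.03 (individual level) and 0.21 (practice level). Respondents: 100 × 10 × 0.75 = 750, so m = 7.5 per practice.

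**Assumed.** The ICC is not in the document. The range shown is 0.02 to 0.20.

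**Step 1: the plan's own figures.** Overall F test of the predictor set, noncentral F with df = (14, N − 15) and λ = f²N.

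- Practice level: N = 100, f² = 0.21, λ = 21, power 80.2%. The stated figure is reproduced.
- Individual level: N = 750, f² = 0.03, λ = 22.5, power 88.5%. The effect detectable with 80% power is 0.0248, and 0.03 needs only N = 624. The stated 0.03 is therefore rounded up, in the safe direction. It is reached with all 750 respondents treated as independent.

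**Step 2: how much clustering the slack absorbs.** Design effect DE = 1 + (m − 1) × ICC = 1 + 6.5 × ICC. Break-even is DE = 750/624 = 1.20, so ICC = 0.20/6.5, about 0.03.

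**Step 3: beyond break-even.** Effective N = 750/DE, put back into the Step 1 formula. This applies the full design effect, which is the worst case and fits predictors that are constant within practice. The power is that of a test that keeps its 5% level. For the type I error of ordinary regression on one such predictor: 2 × [1 − Φ(1.96/√DE)].

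| ICC (assumed) | DE | Effective N | Power at f² = 0.03 | Detectable f² | Type I error, ordinary regression |
|---|---|---|---|---|---|
| 0.02 | 1.13 | 664 | 83% | 0.028 | 6.5% |
| 0.05 | 1.325 | 566 | 75% | 0.033 | 8.9% |
| 0.10 | 1.65 | 455 | 62% | 0.041 | 12.7% |
| 0.20 | 2.30 | 326 | 45% | 0.058 | 19.6% |

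A simulation (100 practices, Binomial(10, 0.75) respondents, 14 predictors, 1,500 runs) gave about 9%, 13% and 20% type I error at ICC 0.05, 0.10 and 0.20, in agreement with the last column.

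**Step 4: clinicians only.** The Participants and setting section takes clinical-behaviour information from clinical staff. With four GPs and three nurses, m = 7 × 0.75 = 5.25 and DE = 1 + 4.25 × ICC. At ICC 0.05, 0.10 and 0.20, DE is 1.21, 1.43 and 1.85, and the type I error is about 7.5%, 10% and 15%. A separate consequence, not due to clustering, is that these outcomes have 525 respondents. Power at 0.03 is then 71% even if all are independent, with a detectable f² of 0.036.

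**Step 5: predictors that vary within practice.** The design effect is then roughly 1 + (m − 1) × ICC(outcome) × ICC(predictor). With a predictor ICC of 0.1 and an outcome ICC of 0.20, this is 1 + 6.5 × 0.02 = 1.13, giving 6.5%; the simulation gave about 6.4%. At outcome ICC 0.05 and 0.10 the simulated rates were about 5% to 6%. Attitude, habit and planning scores would be of this kind if they differ mainly between colleagues.

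**The case against.** The strongest reply is that the study's main analyses are not of this kind. The outcomes are mainly at practice level, individual scores become practice means, and the practice is the unit. Those models are powered separately on 100 practices, including aggregated intention and simulation, and that figure is reproduced. This stands in full: resemblance between colleagues does not inflate type I error there.

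Second, the sentence that names standard regression sits between the remark about practice-level outcomes and the rule for practice means. Nothing says outright that practice-constant predictors will enter an individual-level model without a practice term. The article is a condensed account, and a fuller analysis plan could supply a random effect. This stands in part. The method might be completed elsewhere, but the power figure is fixed here. Individual-level analyses are announced and powered, and the only methods named carry no allowance for practice.

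Third, everything quantitative depends on an ICC that the document does not give, and the full design effect is the worst case. This also stands, so the results are conditional.

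A reader might infer that 80% power is simply not delivered, or that the study's organisational findings as a whole will carry false-positive rates well above 5%. The document supports neither. With 750 respondents the power claim holds up to an ICC of about 0.03. The inflation is confined to practice-constant predictors in individual-level models, and it is small when the ICC is small (6.5% at 0.02).

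**Conclusion.** The point holds in limited form. The individual-level power figure treats clustered staff as independent, and no clustering-aware method is named for outcomes measured on respondents. If the ICC among colleagues is above about 0.03, power for practice-constant predictors drops below the stated 80%, and ordinary regression would test them above the stated 5%, by the amounts in the table. Both results rest on the assumed ICC, on about equal numbers per practice and, for power, on the full design effect.

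Two of the article's conclusions are untouched: the practice-level regressions with their detectable effect of 0.21, and the general statement about effect size. The corrected values of 0.033 to 0.058 still lie between the article's own benchmarks of 0.02 (small) and 0.15 (medium). The point is worth correcting, but it does not threaten the main analyses.

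**What to change.** - **Analysis.** For individual-level outcomes (intention, simulation, self-reported behaviour), specify a random practice intercept or practice-clustered standard errors. Use multilevel or cluster-robust structural equation modelling where the respondent is the unit. Leave the practice-level regressions as they are.
- **Power statement.** Restate the individual-level figure with an explicit ICC range. For example: 80% power to detect f² of about 0.033 to 0.058 for ICC 0.05 to 0.20, for predictors constant within practice with 750 respondents. For outcomes reported by clinicians only, give the figure on the number of clinicians.

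The cost is a slightly less favourable stated effect size and a little more analysis work. No extra practices, staff or data are needed.

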### Statistical analysis

The study will generate data on:

1. Individuals' cognitions about clinical behaviours, clinical conditions, work, team and organisational setting.

2. Organisational structure and function.

3. Clinical behaviours relating to teams of clinicians.

4. Biochemical and physiological measurements that are the consequence of the clinical behaviours, but include consequences of patient physiology and behaviour.

The analysis will explore the relationships between the predictor variables (one and two) and the dependent variables of respondents' intentions to perform behaviours, respondent's behavioural simulation, (both from survey instruments), and the clinical behaviours (three) as well as biochemical and physiological measures (four).

Where appropriate, data will be analysed as the standardised (by list size) number of patients who have had the investigation/procedure of interest performed; standardised number of patients who have their level of the investigation/procedure of interest within the accepted target range. From the patient survey we will calculate the proportion of patients in each practice who have a particular attribute (*e.g*., have been given education or training in self-monitoring).

Where appropriate (*i.e*., more than two items per measure), the reliability of the measures will be assessed prior to analysis using Cronbach's alpha to assess internal reliability and confirmatory factor analysis to identify and discard redundant items. The construct validity of the measures will be assessed prior to analysis by examining correlations between predictor variables that are expected to be similar (convergent validity) and dissimilar (discriminant validity).

We will examine mediating and moderating effects of the predictor variables on the dependent variables. In principle, we will be dealing mainly with dependent variables measured at the level of the practice and predictor variables measured at either the level of the practice or the level of the individual. The theoretical models will be tested using standard multiple regression analysis and structural equation modelling. For predictor variables that are measured at the level of the individual, we will produce a summary statistic for the practice. We will use the practice mean and, in the multiple regression analysis, will weight by practice size. We will explore other summary statistics with weightings reflecting the relevant roles and responsibilities of the respondents.

In addition to the main study analysis, the patient survey will be reported in its own right, including a comparison with the healthcare commission data (available from their website), a comparison of the level of agreement between patients' and health professionals' perceptions and a comparison of patient perceptions and physiological measures of diabetes control.

